### Consent

Six Ambassador Schools with previous experience of taking part in an RCT or other sensitive research have been consulted and involved in developing the evaluation materials and approach to consent that will be used in the Keeping Safe RCT. This has led to the development of information and guidance booklets on the evaluation for parents and teachers, as well as video resources for children.

The process of securing valid informed consent from school stakeholders will begin with recruitment information sessions for school leaders and the provision of resources to enable them to engage their whole school staff and parents. This includes an animated project explainer video; project leaflet; project webpages and links to TV and radio media coverage. Full information on the research will be provided including: what’s involved; why it is being carried out; who will be involved; how the data will be stored and used; measures to safeguard welfare of all participants; and ethical procedures. An RCT infographic will be made available to promote understanding of what randomisation and control group assignment means at school level. Further to the school agreeing to take part, a memorandum of understanding will be used to agree processes, expectations and outputs including procedures for dealing with disclosures of abuse and complaints about the research process/team.

Written ‘process informed consent’ will be sought from all parent, teacher and child participants. Written parental consent will be sought for the participation of all children at baseline and all new school participants (e.g. new intake of primary one children) over the two-year period of the evaluation. Once written parental consent has been provided, an opt-out letter will be sent to parents each year at successive data collection time-points. Once parental consent has been secured, the consent of the children themselves will be sought. Children will watch a specifically designed consent video before completing surveys at each time point. This will inform them about the evaluation and the consent process and will provide practical ways that children can manage their ongoing consent or withdraw at any stage. The video also explains the agency’s confidentiality policy to help the children understand that if they disclose information that gives rise to concerns about their safety or that of another child, the agency may need to link with their school safeguarding team to ensure they are safe. Children will be asked to indicate, by ticking a box on the paper survey or clicking a button on the online survey, whether they consent to take part. The information provided in the explainer video will be presented verbally to children in Primary one and Primary two by a trained volunteer from the agency’s schools service. Children in Primary one and Primary two will be asked to provide verbal assent to their participation. Children with mild-moderate special educational needs and disabilities, and children for whom English is an Additional Language, will be provided with additional support as available in the school to support the securing of their process informed consent to take part.

As the evaluation concerns abuse, it may lead some children to recall past or current sensitive experiences. The ongoing voluntary involvement of children known by the school to have experienced abuse or to be subject to ongoing concerns/cases will be agreed on a one to one basis with the Designated Teacher for Child Protection in the school in conjunction with the child/parents as appropriate. This is important to minimise and prevent personal or social harm. Furthermore, teachers will be provided with a guidance booklet as well as professional development training and resources, to guide them on how best to manage engagement of, and data collection from these children. The project team will be available to offer support to schools and parents on these issues. All children will receive a copy of agency resource booklets on completion of data collection. This is to bring home and help them chat through any concerns with their parents. Participants will have access to a report on the results of the trial once it has been concluded.

## Methods

The evaluation will consist of three rounds of data collection: pre-assessment (baseline), post-assessment one (1 year after baseline) and post-assessment two (2 years after baseline). Data will be collected from children using a composite survey comprising existing and adapted standardised measures across the keeping safe concepts of bullying, physical, sexual, emotional and domestic abuse and neglect as well as anxiety. The content and administration of the survey (online and paper versions available) have been tailored to ensure age and developmental appropriateness and several different versions will be used with different age groups.

Children in Primary four through to Primary seven (ages seven to eleven) will complete online versions of the surveys. Children in Primary three (age six) will complete a paper version in line with their psychomotor development. All children’s surveys consist of self-report measures and will be completed under classroom test conditions supported by classroom teachers and learning assistants. ‘A Guide to Evaluation for Teachers’ booklet will be provided to all classroom teachers to standardise the data collection process across all schools and support school staff collect data from children on these sensitive issues in a manner that safeguards the welfare of the children and is child friendly. The youngest children in Primary one and Primary two (ages four to six) will complete their surveys in one-to-one interview-style sessions with trained volunteers from the non-profit agency schools’ service. Additional school-level administrative behavioural outcome data will be collected via school survey children’s disclosure / teacher reports of children’s maltreatment experiences.

All classroom teachers will be invited to complete a self-report survey with online and paper versions available. Fidelity data on completion of the blended package of training will be collated from the analytics function on the e-learning training programme. Self-reported fidelity to programme implementation in the classroom will be collated using a fidelity monitoring form. Information on school context (size, sector, management type) will also be collected from school administrative data.

All parents will be invited to complete a self-report paper/online survey. Information on parents’/carers’ personal profile (gender) parenting profile (age of children, no of children, relationship to child) home context (Postcode and household income) will be collected via the parent survey.

### Measures

Copies of the outcome measures are available on request from the Principal Investigator.

### Child measures

The children’s surveys will consist of a composite of the measures, outlined below, and a number of versions will be used with different age groups. The children’s measures will be administered at each of the three time points.

#### Demographics

Demographic information will be collected from the children in Primary three through to Primary seven, including gender, age, and primary care giver information.

#### Olweus bullying questionnaire [55]

The two Global Items from the Olweus bullying questionnaire will be used to assess children’s self-reported frequency of bullying perpetration/victimization. These items are culturally appropriate and have been used in the Department of Education survey of bullying in Northern Ireland schools over consecutive years [56]. Olweus’ definition of bullying will be included to promote construct and content validity of these items [31].

#### Children’s knowledge of abuse questionnaire (CKAQ) [57]

The CKAQ is a 33-item self-report questionnaire which will be used to assess children’s (aged six to twelve) knowledge of sexual abuse with a ‘True/False/Not Sure’ format. Responses are scored 0 for incorrect and 1 for correct. Scores will be summed to provide a total sexual abuse ‘knowledge’ score. The CKAQ has strong internal reliability (α = .87) and good test-retest reliability (*r* = .88) [57]. This measure is culturally appropriate and has been used in previous needs assessment research in Northern Ireland schools [42].

#### Revised Children’s manifest anxiety scale 2nd edition (RCMAS-2) [58]

The RCMAS-2 Short Form consists of ten yes/no items and will be used to determine whether programme participation has any negative impact on children’s anxiety levels. A recent US study reported good internal reliabilities in a sample of children aged seven to twelve (α = .78) [59].

#### What if situations test [60]

The What-If Situations Test (WIST) is a six-item scenario-based measure designed to assess six prevention skills: two recognition skills and four personal safety skills. Specifically, they assess children’s (age five to twelve) ability to recognise the appropriateness/inappropriateness of the situation and their ability to refuse, escape, tell and report. The WIST includes a practice scenario, three ‘appropriate request’ scenarios and three ‘inappropriate request’ scenarios. Five additional ‘inappropriate request’ scenarios were added to this measure to include non-contact, online, and peer-to-peer abuse scenarios. Local stakeholders, safeguarding experts and children were engaged in the process of developing the new scenarios. Short seven to ten second animations were developed to accompany each of the 12 scenarios. These will be played via the online survey or on the interactive whiteboard in the classroom for the children in Primary three through to Primary seven (ages six to twelve). Stills from the animations will be used with the children in Primary one and Primary two (ages four to six). Recognition skills are scored 0 for incorrect and 1 for correct. Personal safety skills (inappropriate requests only) are scored from 0 to 2, depending on effectiveness of child’s response. Scores will be summed to provide a total score for each personal safety skill and a WIST total skill score. The original WIST measure has good-strong internal reliabilities (α = .75 to .90) and good test-retest reliabilities (*r*=. 71 to .84) [61].

#### Child-teen witness to woman abuse questionnaire [62]

The ‘Knowledge/Attitudes to Woman Abuse’ sub-scale of the ‘Child/Teen Witness to Woman Abuse questionnaire’ is a 10-item sub-scale that will be used to assess children’s knowledge of domestic abuse using a ‘True/False/Not Sure’ format. This measure is culturally appropriate and has been used in previous needs assessment research in Northern Ireland schools [42]. Responses are scored 0 for incorrect and 1 for correct. ‘Not Sure’ responses will be scored as incorrect. Scores will be summed to provide a total domestic abuse knowledge score.

#### The multidimensional neglectful behaviour scale [63]

Ten items from the original 38-item Multidimensional Neglectful Behaviour Scale will be used to assess children’s knowledge of potentially neglectful scenarios. The items will be adapted and presented as statements (i.e. *It is neglect when…*). Children will respond by answering true, false or not sure. Responses are scored 0 for incorrect and 1 for correct. Scores will be summed to provide a total neglect knowledge score.

#### Self-efficacy sub-scale [64]

The ‘Self-Efficacy Sub-scale’ is a 5-item sub-scale that will be used to assess children’s perceived self-efficacy to keep safe in abusive situations using a ‘1- Really sure I can do it/ 2- I might be able to do it/ 3- Not sure I can do it’ format. An additional 4 items developed through consultation with local stakeholders and safeguarding experts were added to this measure to include situations involving online abuse, cyberbullying, and neglect. Moderate internal reliability (α = .56) was reported for the original measure [64].

An additional response option - ‘*I don’t want to answer this*’ – will also be included for every question to provide children with option of opting out of answering questions that they might find sensitive.

### Parent measure

The parent survey is a composite of the measures outlined below. Parents will be invited to complete this measure at each of the three time points.

#### Demographics

Five items will be used to collect parent and family demographics, including parent/carer gender, relationship to child, number and age of children and home postcode.

#### Parenting and child sexuality questionnaire [65]

Two scales from the Parenting and Child Sexuality Questionnaire [65] were adapted to include topics specific to the Keeping Safe programme. Six items will be used to assess parent’s knowledge of sensitive keeping safe issues; 11 items will be used to assess parents’ confidence to talk to their children about keeping safe. Parents will respond on a 4-point Likert scale from ‘strongly agree’ to ‘strongly disagree’ for knowledge and a 5-point Likert scale from ‘certain I can’ to ‘certain I can’t’ for confidence. Scores will be summed to provide total ‘knowledge’ and total ‘confidence’ scores. Good-strong internal reliabilities were reported for the original knowledge and confidence scales (α = .77 and .95 respectively) [65]. A further four items will be used to assess parents’ current and future confidence to talk to their children about keeping safe [66].

### Teacher measure

The teacher survey is a composite of the measures outlined below. Teachers will be invited to complete this measure at each of the three time points.

#### The teacher willingness to teach sexual health education questionnaire [67]

The teacher comfort subscale will be used to assess teachers’ knowledge and comfort levels in relation to teaching sensitive keeping safe messages. It has been adapted to include topics specific to the Keeping Safe programme. Teachers will respond on a 5 point Likert scale from ‘extremely comfortable’ to ‘not at all comfortable’ for comfort and ‘extremely knowledgeable’ to ‘not at all knowledgeable’ for knowledge. Scores will be summed to provide a total ‘comfort’ score and total ‘knowledge’ score.

#### The survey on perceived confidence in, and attitudes towards, approaches to teaching and learning about sensitive issues in Health & Personal Development [68]

Twelve items from part 2 of the survey will be used to assess teachers’ confidence in managing sensitive issues. This measure has been adapted to focus on the classroom management issues that pertain to the Keeping Safe programme. Teachers will respond on a 5 point Likert scale from ‘strongly agree’ to ‘strongly disagree’. Scores will be summed to provide a total ‘confidence’ score.

#### School-level environment questionnaire – South Africa (SLEQ-SA) [69]

Thirty-five items across six sub-scales will be used to assess teachers’ perceptions of their school culture. Teachers will indicate on a 5 point Likert scale from ‘never’ to ‘always’ how often different practices take place in their school. Internal consistencies for the sub-scales range from α = .69 to α = .92.

### Retention

The evaluation team will endeavour to maximise participant retention throughout the course of the trial. Schools will be provided with resources including templates of school development plans and programme calendars to demonstrate how they can incorporate the programme and evaluation into their own school development planning processes. Schools will also be supported to engage and secure parental support through information sessions and parent evenings. Technical support will be provided to promote programme implementation in intervention schools. Advice and support will also be provided to assist schools with the completion of the teachers’ and children’s surveys in school. Opportunities to seek additional information and support will be available to teachers and parents to promote their retention within the trial and completion of evaluation surveys. Reminder opt-out consent letters will be issued to parents at the beginning of each round of data collection to ensure they remain fully informed and engaged throughout. Regular communications via e-mail and newsletters will be used to update schools on the trial and acknowledge their ongoing support. While every effort will be made to promote school engagement and retention throughout the trial, participants may withdraw at any time for any reason. It will not be possible to carry out follow-up assessments with any participants who have withdrawn from the study.

### Confidentiality

All outcome data will be identified by a unique ID only to ensure participant confidentiality. The unique IDs will also be used to enable matching of data across the timepoints of the trial. An electronic file containing participant names and unique IDs will be stored on a secure network to which only the evaluation team will have access. No identifying information will be recorded on completed data forms. All data collected will be stored anonymously with categorical labels being used to identify according to stakeholder group, school type, school sector, age of pupil, rural urban school. Categorical variables will be held separately to ensure that the statistician is unable to identify individual cases or responses within the data set.

In accordance with agency ethics guidelines, all completed forms (online and paper) will be reviewed for child protection concerns. If a concern or disclosure is identified, the concern, along with the unique ID will be passed to the Programme Development and Implementation Lead who will decide the action required. If necessary, the unique ID can be used to identify the child to whom the concern relates in order to facilitate contact with the child’s school and ensure appropriate safeguarding procedures are put in place. All participants will be made aware of this prior to the start of the evaluation. Any documentation containing identifying personal information, including consent forms will be stored in a locked cabinet to which only the evaluation team will have access. Results from the trial will be reported in a way that ensures no individual school, teacher, parent or child is identifiable.

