**Methods/design:**

A cluster Randomised Controlled Trial (RCT) will be conducted with children in 80 schools over a two-year period. The unit of randomisation is the school. Schools will be allocated to intervention or wait-list control groups using a computer-generated list. Data will be collected at three time points: baseline, end of year one, and end of year two of programme implementation. Primary outcomes will include: children’s understanding of key programme concepts, self-efficacy to keep safe in situations of maltreatment, anxiety arising from programme participation, and disclosure of maltreatment. Secondary outcomes include teachers’ comfort and confidence in teaching the programme and parents’ confidence in talking to their children about programme concepts.

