### Blinding

While it is not possible to blind trial participants in schools or programme facilitators delivering the Keeping Safe training to schools, outcome data will be obtained through self-report measures for teachers, parents and Primary three to Primary seven children thus reducing potential outcome assessor bias. Agency volunteers who will be collecting one to one interview data from Primary one and Primary two children will be blinded to school allocation status. Data processors and the trial statistician will also be blinded in this regard.

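### The primary disclosure outcome is drawn from school safeguarding records, and the article does not separate out concerns that the trial's own form screening may pass to those schools

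*Protocol article*

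**What the plan says.** The abstract's Methods/design paragraph lists among the primary outcomes "anxiety arising from programme participation, and disclosure of maltreatment". The Primary objectives section takes disclosure from safeguarding data held by the school, covering concerns, disclosures and referrals. The Methods section gives the collection route: "Additional school-level administrative behavioural outcome data will be collected via school survey children’s disclosure / teacher reports of children’s maltreatment experiences".

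The Confidentiality section says that "all completed forms (online and paper) will be reviewed for child protection concerns". It continues: "If a concern or disclosure is identified, the concern, along with the unique ID will be passed to the Programme Development and Implementation Lead", and it is the Lead who decides what is done. If necessary the ID is used to identify the child, "in order to facilitate contact with the child’s school and ensure appropriate safeguarding procedures are put in place". The Consent section describes the same route in what children are told: "the agency may need to link with their school safeguarding team to ensure they are safe".

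The Blinding section names the volunteers who interview the youngest children, and then adds: "Data processors and the trial statistician will also be blinded in this regard". The Lead does not appear there.

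**The concern.** The trial's measurement can feed its own outcome. A concern written on a survey form may be sent to a school, and a school that receives it may well record it as a safeguarding concern. The school survey then returns that record as outcome data. The article has no rule or data item that would tell such a record apart from one that arose in ordinary school life.

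The Discussion treats school disclosure data as the behavioural evidence on the programme. An event that exists only because the trial screened a form would not occur when the programme runs outside a trial. If such events are equally common in both arms, they add background. If they are not, they add a difference. Inequality is plausible after baseline: the Being Safe theme in Table 1 teaches children to seek help and to keep telling, so programme children may write more on their forms. The decision on what goes forward rests with someone whose title suggests a programme role and whose masking is not stated.

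**Working it through.** **1. Does the path exist in the text?** Set side by side: all forms are screened, with no distinction by arm (Confidentiality); there are three survey rounds (Methods); concerns may go to the school (Confidentiality, Consent); the outcome is the school's own safeguarding data (Primary objectives, Methods). No section excludes or flags events by source. The path is open. How many events use it is not stated.

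**2. The plan's own figure.** The Sample size section gives 40 schools per arm, 150 surveys per school, an intra-class correlation of 0.2, 80% power, a control rate of about 5% and a detectable difference of 2.7 points.
- Effective children per arm = 40 × 150 / (1 + 149 × 0.2) = 6,000 / 30.8 = 194.8. Solving for 80% power at two-sided 5%, without covariate adjustment, gives 8.1 points, not 2.7.
- For 5% v 7.7%, n = [1.96√(2 × 0.0635 × 0.9365) + 0.8416√(0.05 × 0.95 + 0.077 × 0.923)]² / 0.027² = 1,280 effective children per arm. That is a design effect of 6,000 / 1,280 = 4.69 and an intra-class correlation of (4.69 − 1) / 149 = 0.025.

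So 2.7 does not follow from the listed inputs. That is a separate matter. Below, 5% v 7.7% with 80% power is taken at face value, with 1,280 effective children per arm.

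**3. Equal contamination.** Assume that a proportion c of children in each arm has a survey-originated record, independent of other records. The observed rate is then p + c − pc, and the difference is 2.7 × (1 − c). Power = Φ{[d√1,280 − 1.96√(2p̄q̄)] / √(p₀q₀ + p₁q₁)}, where d is the observed difference, q = 1 − p and p̄ is the mean of the two rates.

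| c (assumed) | Control | Intervention | Difference, points | Odds ratio | Power |
|---|---|---|---|---|---|
| 0 | 5.00% | 7.70% | 2.70 | 1.59 | 80% |
| 0.5% | 5.48% | 8.16% | 2.69 | 1.53 | 77% |
| 1% | 5.95% | 8.62% | 2.67 | 1.49 | 74% |
| 2% | 6.90% | 9.55% | 2.65 | 1.42 | 68% |
| 5% | 9.75% | 12.31% | 2.56 | 1.30 | 54% |

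The odds ratio of 2.95 that the Sample size section cites from earlier studies (5% v 13.4%) would be observed as 2.64 at c = 1% and 2.41 at c = 2%.

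**4. Unequal contamination, no programme effect.** Two illustrations, both assumed.
- Survey-originated records add 1 point in control and 2 in intervention: 6% v 7%, odds ratio (0.07 / 0.93) / (0.06 / 0.94) = 1.18.
- The same share of children is flagged in both arms, but 80% v 50% of concerns are forwarded. The false difference is 0.95 × c × (0.80 − 0.50), which is 0.29 points at c = 1% and 0.57 points at c = 2%.

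**The case against.** The strongest reply is that the article is silent, and silence is not error. It does not say that survey-originated contacts are counted. The school survey form is not shown, and counting rules are often left to the full protocol or the analysis plan. This stands against the reading, which a reader might infer, that the outcome does count concerns created by the trial. It does not remove the point: both the outcome source and the screening route are fixed here, and a later plan can separate the events only if their source was recorded at the time. The Data management section mentions a queries log, but does not tie it to safeguarding contacts or to this outcome.

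A reader might also infer that an unblinded Lead will bias the comparison. The documents do not support that. The Lead's knowledge of allocation is implied by the role, not stated. The concern arrives with an ID, and the child is identified only if necessary. Whether the ID reveals the school is not said.

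Three further objections hold:
- The Randomisation section places allocation after baseline data collection, so baseline concerns cannot differ by arm through the programme.
- The volume may be small. Forwarding is conditional, most child measures test knowledge, skills or self-efficacy, and only the two bullying items ask directly about experience of maltreatment. Some children flagged may already be known to the school.
- The disclosure target in the Sample size section is a percentage-point difference, and equal contamination hardly moves it.

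Finally, removing survey-first events is not neutral. A child who tells through the form might otherwise have told a teacher.

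**Conclusion.** The point stands as a gap in source identification, with medium confidence. Survey-originated concerns after baseline could enter a primary outcome, possibly unequally by arm, and the article provides no means to see or separate them. It also does not state whether the person deciding on action is blinded.

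At an assumed 1% to 2% of children in each arm, the difference in points is almost unchanged, the odds ratio falls from 1.59 to 1.49 or 1.42, and power falls from 80% to 74% or 68%. These figures rest on the protocol's 5% v 7.7% taken at face value, on independence from other records, and on a rate for which the article gives no basis. The unequal case shows what could happen; nothing in the article shows that it will. A claim of demonstrated bias, or of a material loss in the percentage-point effect from equal screening, would go beyond the documents.

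**What to change.** Leave the safeguarding pathway as it is. Then:
- keep a dated log, by school, of every contact that began with a trial survey form, and add an item on the source of each event to the school survey;
- report these contacts by arm;
- analyse disclosure both with and without them, and fix in advance which version is primary;
- withhold school allocation from the concern report where the action allows, or state what the decision-maker knows of allocation.

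The cost is one log field, one survey item and one extra analysis. Excluding survey-first events may drop some disclosures that would otherwise have been made to staff, possibly unequally by arm, so both versions should be shown. The log has to run prospectively, because the source of an event may not be recoverable from school records afterwards.
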